**Ethics and dissemination:**

Ethical approval for this clinical trial has been obtained from the West of Scotland Research Ethics Service. The trial will commence in September 2019 for a duration of 2 years. Results will be presented at local, national and international meetings, as well as submission for publication to peer-reviewed journals.

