## Study methods and analysis

### Study design

This study is a prospective observational cohort hybrid implementation and effectiveness study.^26^ It will be performed according to the UK Policy Framework for Health and Social Care Research (2020).^27^ The clinical intervention component is regarded as a phase IV adoption study. Data visualisation to facilitate guideline-based care, supported self-management and home NIV are evidence-based COPD interventions.

In this study, we will evaluate the adoption of digitally integrated remote management service innovations to support routine clinical care. Implementation of these will be evaluated and the digital innovations will be iterated to optimise them, based on user experience accrued during the study. We will acquire a consented dataset for trial endpoint analysis including exploratory machine learning-based predictive modelling. The machine learning analysis will also allow us to prioritise data inputs for follow-up study.

Secondary outcomes for the RECEIVER cohort will be compared with those from matched cohorts of patients acquired from the NHS GG&C SafeHaven dataset. Ethics approval is in place to access this large database of de-identified data, to establish a control cohort from a historical time series and a RECEIVER trial concurrent time series. These cohorts will be matched for demographics, COPD severity and hospital admission frequency with the RECEIVER cohort.

We will conduct a substudy of additional baseline and follow-up physiological measurements (oscillometry, parasternal electromyography (EMG), home pollution monitoring) in patients in whom it is feasible to obtain these during their hospital admission and/or hospital attendance alongside their routine clinical care.

Additionally, we will conduct a substudy of clinical users, with platform tracking analytics to measure clinician time spent on the platform, and user experience data. Clinical team members involved in the delivery of patient support using the digital service will be eligible for inclusion and appropriate consent will be sought. The qualitative components will be acquired through semistructured group or 1:1 interviews conducted by trained members of the research team. Thematic analysis will be performed. Anonymised transcripts will be coded, and themes generated from the codes. Themes will be discussed within the research team to reach agreement and add rigour.

An overview of the study design is provided in figure 2.

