### Subsequent assessments

Participants will be recruited into the digitalised service model over a 12-month period. Observation of secondary endpoints will be continued over the 12-month period following recruitment. Participants who are recruited will subsequently continue within the digital service model beyond the trial period, either until ongoing procurement of the service infrastructure is established, or transition to alternative equivalent service model is completed.

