### Definition of end of trial

The end of trial will be when the last participant has completed follow-up, 12 months after recruitment.

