## Statistics and data analysis

Secondary outcomes in the RECEIVER observational cohort will be compared with matched retrospective data from de-identified linked datasets of historical control and contemporary control high-risk patients with COPD. These will comprise of patients identified from coding and admission data as having had severe exacerbation of COPD between 1 January 2010 and 30 April 2019 (historical cohort) and between 1 July 2019 and 30 June 2020, excluding participants enrolled in the RECEIVER Study (contemporary control). The historical control dataset will contribute to machine learning models development. Secondary outcome analysis will be separately compared between the RECEIVER cohort, historical cohort and contemporary control cohort. This component of the study is also separately registered with dataset access approval from NHS GG&C SafeHaven LPAC.

The clinical endpoint data will be reported as a proportion and 95% CI for that outcome, calculated by Kaplan-Meier method. Demographic data will be presented as mean and SDs, or medians and IQRs as appropriate. Correlation, t-test, analysis of variance and effect size analyses will be used as appropriate for secondary endpoint analysis, comparing results of clinical endpoint and patient-centred outcomes with NIV therapy and supported self-management parameters.

Machine learning ensemble methods will be used to develop binary classification problems for patient risk. Precision, recall, accuracy and C-statistics of the receiver operating characteristic curve will be used to evaluate model performance.

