## RECEIVER trial qualitative substudy: protocol addition and amendment September 2020

Following the outbreak of the COVID-19 pandemic, the digital service model established in the RECEIVER trial was adopted for routine clinical care in NHS GG&C. This was to mitigate for the anticipated COVID-19 impacts on routine COPD care, with concern about increased winter admission risks and continued requirement to maintain social distancing with vulnerable/shielding patients. Process for invitation and remote enrolment in the COPD digital service, via support website, has been established. People with COPD are enrolled following clinician referral or via invitations sent by Short Message Service (SMS) and letters to known patient cohorts.

Patient utilisation, clinical and service outcomes in this scale-up cohort will be evaluated in parallel with the data from the RECEIVER trial. These analyses will be conducted on de-identified data derived from NHS GG&C SafeHaven. There is separate ethics approval and protocol for these analyses.

It is relevant to gather user experience of the remote invitation and enrolment process to the digital service model and determine whether there are different experiences based on the recruitment source (via clinical trial, via invitation and website registration, via clinician referral). A sample of convenience of people who have enrolled in the COPD digital service via this scale-up service model will be established by the clinical team. They will be approached by the clinical team via the digital service messaging interface. People expressing an interest in undertaking semistructured interviews about their service experience will be sent a RECEIVER substudy patient information sheet and consent form. These people would then be contacted by one of the study investigators with the consent form discussed and completed by telephone, avoiding COVID-19 context risk of face-to-face contact for vulnerable individuals. The consent form with investigator signature would be mailed to the participant. Semistructured interviews would then be scheduled and conducted by telephone or video call, using NHS GG&C Attend Anywhere platform.

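### Contemporary controls may join the rolled-out digital service during follow-up with no stated rule for handling them, and the historical comparison cannot separate the service from the pandemic period.

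*Protocol article*

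**What the plan says.** All references are to the protocol article.

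- **Timing of the trial.** The abstract states: "The trial will commence in September 2019 for a duration of 2 years". Under Subsequent assessments: "Participants will be recruited into the digitalised service model over a 12-month period". Under Definition of end of trial: "The end of trial will be when the last participant has completed follow-up, 12 months after recruitment".
- **Controls.** Study design says the SafeHaven data will be used "to establish a control cohort from a historical time series and a RECEIVER trial concurrent time series". It lists demographics, COPD severity and hospital admission frequency as matching factors; calendar time is not among them.
- **Control dates.** Statistics and data analysis takes patients with "severe exacerbation of COPD between 1 January 2010 and 30 April 2019 (historical cohort"), and for the second cohort "between 1 July 2019 and 30 June 2020, excluding participants enrolled in the RECEIVER Study (contemporary control"). Each control cohort is to be compared with the trial cohort separately.
- **Roll-out.** The section on the September 2020 amendment says that, after the COVID-19 outbreak, "the digital service model established in the RECEIVER trial was adopted for routine clinical care in NHS GG&C". Entry is by clinician referral or by invitation to patients already known to the service. These users are to be evaluated on SafeHaven data in parallel with the trial, under a separate protocol and ethics approval.
- **What depends on the controls.** Table 1 compares exacerbations, unscheduled care, mortality, bed days and treatment uptake with these cohorts. The primary endpoint is use of the service and needs no control.

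**The concern.** A control group should show what happens without the intervention over the same period. Two features of the stated rules work against that.

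1. **Roll-out into the contemporary controls.** A health-board patient with a coded severe exacerbation between July 2019 and June 2020 who did not join the trial is a plausible candidate for the scale-up invitation. The control rule neither excludes such a patient nor ends their control time on joining. Followed literally, it counts service users as untreated controls, which would tend to shrink any difference.
2. **Period in the historical comparison.** Historical patients were followed almost wholly before the pandemic and trial participants mostly during it. Matching on the listed factors cannot remove a period effect when the periods barely overlap.

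These are the only comparative clinical analyses in a study described as a hybrid of implementation and effectiveness. The cost analysis also relies on a projected fall in admissions relative to the previous service model.

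**Working it through.** **Step 1. Reproduce the stated duration.** 12 months of recruitment + 12 months of follow-up = 24 months, which agrees with the stated 2 years. A start on 1 September 2019 puts recruitment at 1 September 2019 to 31 August 2020 and the end of follow-up at about 31 August 2021.

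**Step 2. Overlap of the contemporary window with recruitment.** Only the start month is given, so both ends of September are tried.

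| Assumed start | Shared days | Overlap | Offset at each end |
|---|---|---|---|
| 1 September 2019 | 304 of 366 | 304/366 = 83% | 62 days |
| 30 September 2019 | 275 of 366 | 275/366 = 75% | 91 days |

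**Step 3. Contemporary-control follow-up after roll-out.** Assume one entry per day from 1 July 2019 to 30 June 2020 (366 days) and 365 days of follow-up each. Total follow-up = 366 × 365 = 133,590 days. The roll-out date is not given; the section reporting it is dated September 2020.

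- From 1 September 2020: the last entrant contributes 302 days after that date, the previous one 301, and so on to 1. Sum = 302 × 303/2 = 45,753. Share = 45,753/133,590 = 34%.
- From 1 October 2020: sum = 272 × 273/2 = 37,128. Share = 28%.
- From 1 June 2020: 30 entrants contribute all 365 days, and the other 336 contribute 29 to 364 days. Sum = 10,950 + 66,024 = 76,974. Share = 58%.

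Exposed control time = share × uptake. Uptake is not given. Purely for illustration, assumed uptake of 20–50% reached at once gives 0.34 × 0.2 = 7% to 0.34 × 0.5 = 17% from 1 September, and up to 0.58 × 0.5 = 29% from 1 June.

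**Step 4. Follow-up in the pandemic period.** The last historical index date is 30 April 2019, so 12-month follow-up ends by 30 April 2020. The documents give no pandemic start date, so it is varied. Entry is uniform, from 1 September 2019 for the trial.

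| Assumed cut date | Trial | Contemporary | Historical |
|---|---|---|---|
| 1 January 2020 | 94% | 87% | 0.6% |
| 1 March 2020 | 88% | 78% | 0.1% |
| 1 April 2020 | 83% | 72% | 0.03% |

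**Step 5. What a period effect alone could do.** If admission rates change by a fraction c after the cut, a service with no effect shows a rate ratio of (1 + c × trial share)/(1 + c × control share). With the 1 March cut and assumed values of c:

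- c = −0.2: versus historical 0.825/0.9997 = 0.83; versus contemporary 0.825/0.845 = 0.98.
- c = −0.5: versus historical 0.562/0.999 = 0.56; versus contemporary 0.562/0.612 = 0.92.
- c = +0.2: versus historical 1.175/1.0003 = 1.17; versus contemporary 1.175/1.155 = 1.02.

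The period problem is potentially large for the historical comparison and small for the contemporary one. Its sign follows the assumption about c.

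**The case against.** The case for leaving the plan alone has several parts.

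- **Secondary analyses in a feasibility study.** The primary endpoint is untouched, and Study limitations admits bias and disclaims definitive proof. This stands and lowers the severity. But the acknowledgement is general: it names neither roll-out nor period, and the comparisons are still planned.
- **Other documents may deal with it.** The control component is separately registered, and scale-up users have their own protocol. That suggests they can be identified, and nothing says they will knowingly be analysed as controls. This stands in part: a handling rule may exist elsewhere. Even so, the article states an explicit control definition with a single exclusion, and that definition admits service users.
- **A pre-pandemic historical cohort is not a mistake in itself.** True. It is paired with a contemporary cohort and reported separately. What remains is how it should be read.
- **Censoring at joining may be informative.** Joiners arrive by referral or invitation, and the planned Kaplan-Meier method assumes non-informative censoring. This stands, and the fix allows for it.

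Three stronger readings are tempting but unsupported.

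- A reader might infer that the contemporary control is not concurrent at all. Step 2 shows that most of the window is shared. Nor can the unshared part be read as the fraction of participants without a same-period control. Controls are dated by exacerbation, whereas participants may enrol up to 12 months after theirs and the home NIV cohort is defined without one.
- A reader might infer that roll-out affects both comparisons. Historical follow-up ends by 30 April 2020, before any roll-out date considered here, so roll-out bears on the contemporary comparison only.
- A reader might infer that the pandemic must flatter the service. The documents do not show this. Their only directional remark is a concern about increased winter admission risk.

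**Conclusion.** The point holds for the secondary clinical comparisons and should be fixed. It does not touch the primary endpoint.

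- **Contemporary comparison.** The stated rule lets controls receive the intervention during follow-up. About a third of their follow-up (34%) lies after 1 September 2020, assuming uniform entry, 12 months of follow-up and availability from that date. An earlier or later roll-out moves the figure (28–58% for the dates tried). The likely effect is dilution, of unknown size because uptake is not given. The 2–3 month offset and the absence of calendar time from the matching factors are lesser faults.
- **Historical comparison.** Period and service are confounded almost completely: 83–94% of trial follow-up falls after the assumed pandemic cut dates, against at most 0.6% of historical follow-up. The rate ratios in Step 5 are illustrations under assumed changes in admissions, not estimates, and the direction of bias is unknown from the documents.

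**What to change.** For the secondary clinical comparisons:

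1. Set the contemporary window to the actual first and last recruitment dates, and add calendar month of index to the matching factors. State which date serves as a participant's index, since controls are dated by exacerbation.
2. Censor each contemporary control on the date of joining the scale-up service. Do not delete joiners retrospectively, because that selects on events after index: a patient must survive to roll-out in order to be removed.
3. Add a sensitivity analysis that leaves joiners uncensored, because joining may be related to prognosis. Report how many controls joined and when.
4. Present the historical comparison as descriptive pre-pandemic context, and name the period confounding in the limitations.

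Truncating both groups at roll-out is optional. With a 1 September 2020 cut, about 50% of trial follow-up would be lost under uniform entry. That leaves about 6 months on average and makes the 12-month endpoints incomplete for most participants.

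**Cost:** an amended SafeHaven data request, including scale-up joining dates, revised analysis wording, and some control follow-up lost to censoring. The planned parallel SafeHaven evaluation of scale-up users suggests that the joining dates can be obtained.

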### Study population

People with high-risk COPD attending secondary care in the North and South Sectors of NHS GG&C will be screened for inclusion in this study.

Inclusion criteria:

Confirmed diagnosis of COPD, established prescreening or at screening, defined as per Global Initiative for Chronic Obstructive Lung Disease (GOLD) 2020 guidelines.^6^Home NIV cohort: hypercapnic respiratory failure and/or sleep disordered breathing, meeting established criteria for provision of home NIV.Exacerbation cohort: presentation within last 12 months with severe or life-threatening exacerbation of COPD, defined as per GOLD 2020 guidelines.^6^Participant or close contact who has daily access to smartphone, tablet or home computer with internet access.Informed consent.>18 years of age.

Exclusion criteria:

Inability to comprehend informed consent.Communication barrier precluding use of COPD digital service.

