### Machine learning analysis and predictive modelling

These analyses will be conducted post hoc, using the clinical data obtained from the RECEIVER trial COPD platforms, alongside EHR data in historical and contemporary control patients from NHS GG&C SafeHaven. The anticipation is that following analysis of the study data, we will be able to judge the feasibility and accuracy of using predictive model outputs at a service or individual patient level. This may lead to the subsequent development and evaluation of artificial intelligence(AI)-based clinical decision support tools. Relevant clinical investigation/medical device trial(s) of these would be proposed and designed. The data from the RECEIVER trial would not be used directly to support clinical validation of any subsequently developed medical device.

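### RECEIVER participants are removed from the contemporary control only, so some can also be historical controls, and late historical records may include up to about 8 months on the digital service

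*Protocol article*

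**What the plan says.** The section Statistics and data analysis defines both control cohorts in one sentence. The historical cohort consists of patients coded as "having had severe exacerbation of COPD between 1 January 2010 and 30 April 2019 (historical cohort"). The contemporary cohort has its event "between 1 July 2019 and 30 June 2020, excluding participants enrolled in the RECEIVER Study (contemporary control"). The exclusion belongs to the second cohort, and no other section removes participants from the first.

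Study design says of the controls: "These cohorts will be matched for demographics, COPD severity and hospital admission frequency with the RECEIVER cohort". Under Study population, the exacerbation cohort enters on "presentation within last 12 months with severe or life-threatening exacerbation of COPD". The Abstract gives a September 2019 start. Subsequent assessments gives 12 months of recruitment and 12 months of observation after it. Table 1 lists bed days over the 12 months before and after among the outcomes compared with both SafeHaven cohorts.

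The historical data have a second use: "The historical control dataset will contribute to machine learning models development". The section Machine learning analysis and predictive modelling describes work "using the clinical data obtained from the RECEIVER trial COPD platforms, alongside EHR data in historical and contemporary control patients", after which "we will be able to judge the feasibility and accuracy of using predictive model outputs at a service or individual patient level".

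**The concern.** Participants and controls come from the same health board, and RECEIVER recruits people prone to repeated severe exacerbations. Some participants will therefore meet the historical definition. Three things follow if the text is applied as written.

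- **Shared person-time.** A late historical index event can have follow-up that continues after the person joined RECEIVER. Time on the service, and any admissions in it, would then count as historical control experience and pull the contrast toward zero.
- **Shared people.** The t-tests and analysis of variance named in the plan treat the groups as independent, although some people may be in both. The bed days before a participant's enrolment may also be the bed days after that same person's historical index.
- **Shared records in the models, conditionally.** If models developed partly on historical data are then assessed in RECEIVER participants, some of those participants' own records may be in the development set, and performance could look better than it is.

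**Working it through.** The plan states no figure for overlap, so there is none to reproduce. The check is date arithmetic followed by ranges under stated assumptions.

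**Can a participant be in the historical cohort?** A person enrolled on 1 September 2019 may qualify on an event back to 1 September 2018. Events from that date to 30 April 2019 lie inside the historical window. The last enrolment date that can rest on such an event is 30 April 2020. A participant recruited on a later event may also have an earlier one inside the window.

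**Largest shared follow-up.** Assume 12 months of historical follow-up (inferred from Table 1; the statistics section gives no length).
- An index of 30 April 2019 plus 12 months ends on 30 April 2020.
- Enrolment on 1 September 2019 leaves 242 days; 242/30.44 = 7.95 months.
- Enrolment on 30 September 2019 leaves 213 days; 213/30.44 = 7.0 months.

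**How many participants?** Assume enrolment uniform over 12 months from 1 September 2019 and a lag from exacerbation to enrolment uniform over 0 to 12 months. The qualifying event falls in the historical window when the lag exceeds time since 1 September by at least 4 months.
- Share: (8 × 8 / 2) / (12 × 12) = 32/144 = 22%. Mean overlap: 8/3 = 2.7 months. A simulation in days gave 21.8% and 2.66 months.
- Screening and eligibility assessment expects most recruitment during the index admission, where the lag is about zero. If 50% to 90% are recruited that way, the share is 0.50 × 21.8% = 10.9% to 0.10 × 21.8% = 2.2%. That is about 44 to 9 of 400, taking all 400 as entering by the exacerbation route.
- This counts only the qualifying event. Suppose instead that severe exacerbations follow a Poisson process at 1 per year and the latest event in the window is the historical index. The chance of an event both in the window and within 12 months before enrolment, averaged over enrolment dates, is (1/12) × [8 − 12 × (1 − e^(−8/12))] = 0.667 − 0.487 = 0.18, or 0.18 × 400 = 72. Indexing on the first event would lower this.

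**Size of the dilution.** Let f be the share of matched controls affected, m the shared months, and 1.0 admission per patient-year the reduction projected under Sample size. Dilution = f × (m/12) × 1.0.
- f = 0.10, m = 8: 0.067.
- f = 0.10, m = 2.7: 0.10 × 2.7/12 = 0.022.

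The value of f is assumed. It is a share of matched controls, who are drawn from a 9.3-year pool, and not a share of participants.

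**Standard errors.** For two equal groups with a fraction f of people in both and within-person correlation r, the true SE divided by the unpaired SE is √(1 − f·r).
- f = 0.1, r = 0.3: √0.97 = 0.985.
- f = 0.5, r = 0.5: √0.75 = 0.866.

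With positive correlation the unpaired standard error is too large.

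**The case against.** The strongest reply is that leaving participants in the historical cohort is not itself a mistake. Deleting people because they later enrolled would condition on surviving to enrolment and remove frequent exacerbators. That stands, and the fix therefore does not rest on deletion. It does not answer the shared person-time, which needs a rule of its own.

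A second reply is that censoring, matching and clustering are details for an analysis plan or for the separately registered SafeHaven component, neither of which is shown. This has some force. The article does, however, state an overlap rule and apply it to only one of the two cohorts exposed to overlap.

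Third, the stakes are limited. The primary endpoint is utilisation, the contemporary comparison is separate and unaffected, and Study limitations disclaims definitive proof. All of this stands.

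A reader might also infer more than the text supports:

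- **That model performance is inflated.** No evaluation set or data split is named. Questionnaire and wearable inputs come from the RECEIVER platform, so models using them cannot be built on historical records alone. Leakage is possible, not established.
- **That 120 to 320 of 400 participants are affected.** That range (400 × 0.30 and 400 × 0.80) comes from an assumed 30% to 80% with a coded event in the window. It counts membership of the pool; a person's records from before enrolment are untreated time and not in themselves a bias.
- **That ignoring the pairing gives falsely narrow intervals.** With positive within-person correlation it does the reverse.
- **That matching selects people's own earlier records.** It may, but the earlier record belongs to a younger person whose severity and admission frequency may differ.

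**Conclusion.** The point holds in a limited form. As written, a RECEIVER participant can also be a historical control, and nothing in the article prevents on-service time from counting as historical control time. The maximum is about 8 months, in the extreme case of the latest index date and the earliest enrolment; the average under uniform assumptions is about 2.7 months. The resulting dilution is probably modest, about 0.02 to 0.07 admissions per patient-year if 10% of matched controls are affected, and unpaired tests would lean conservative. Both effects work against finding a benefit in the historical comparison.

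This rests on 12-month historical follow-up, which is inferred, and on assumed shares, because the article gives neither. The modelling part is conditional on performance being reported in RECEIVER participants. The change is worth making because it costs so little, not because the distortion is likely to be large.

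**What to change.** Use the linkage already needed for the contemporary exclusion to flag RECEIVER participants in the historical data, then state the following:

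- **Follow-up.** Censor historical follow-up at RECEIVER enrolment and express outcomes per time at risk, as Table 1 already does for early death. Count the admission at which enrolment takes place before censoring. Alternatively, end the historical index window at about 31 August 2018, so that 12-month follow-up closes before September 2019. That gives up 8 of 112 months of index dates (7%) and avoids censoring that is itself tied to an admission. Either option brings shared on-service time to zero.
- **Matching and variance.** Do not match a participant to their own record. Where a person remains in both cohorts, cluster or bootstrap by person. Report a sensitivity analysis without RECEIVER members, noting that it conditions on survival to enrolment.
- **Models.** If performance is reported in RECEIVER participants, split development and evaluation data by person, so that their historical records are not in the development set.

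The cost is one identity flag, a few lines of analysis code, and slightly fewer control months and development records.
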